# ADVERSE EVENTS

There may be a very small increased risk of falling as a result of walking practice and this small risk is stated clearly in the patient information sheet. Every effort will be made to minimise the risk of falls through training the patient and having therapists next to patients at all times. We do not expect any other risks of taking part in the study. Therefore, it is reasonable to collect only targeted treatment-related adverse events and serious adverse events such as ‘falls leading to injury requiring a hospital or GP visit’. Should such an event occur, an adverse event form (Appendix 11) will then be completed by the relevant therapist (forms can also be downloaded from the trial website). Participant fatigue which requires only momentary rest and following which the training session resumes will not be classed as an adverse event and will not require reporting but will be documented through any resulting reduction in treatment time.

## Trial Treatment / Intervention Related SAEs

Should training be halted, the participant is asked to rest (sitting or standing) while BP and HR are monitored and training will resume only when vital signs have returned to within an acceptable range and excessive dyspnea or chest pain have resolved. If any of these conditions persist after rest, the patient's primary physician is called and the patient referred for evaluation. If the patient complains of angina at rest, loss of consciousness occurs, or cardiac arrest, emergency medical services through 999 are called immediately. All therapists are CPR certified and aware of signs of cardiac complications.

Training sessions will also be halted in the event of a fall. All therapists are trained in first aid and manual handling and will assess the participant for injury. Should the fall be injurious and bone fracture, cardiac or neurological event is suspected, emergency medical services through 999 are called immediately. Should the fall be non-injurious the therapist will aide the participant to an upright position, monitor vital signs as outlined above and resume the training session if and when both the therapist and participant deem appropriate i.e. after rest or on the next planned treatment day.

### Participant removal from the study due to adverse events

Participants will be removed from the study following an AE if treating medical team indicate that the participant is no longer able to tolerate walking practice.

#

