### Baseline Data

Baseline assessments will be conducted **PRIOR** to randomisation as recommended in guidelines for good practice in RCTS (MRC), therefore reducing possible recruitment bias.

Prior to randomisation, patients and the clinician will fill out a series of questionnaires (see Table 1) including:

Primary care staff recorded patient demographics (Appendix 1):

1. Known stroke or TIA. Date of stroke, side of stroke, type of stroke – if recorded on the Demographic Front Sheet

3. Known medical history: premorbid conditions such as a concurrent progressive neurologic disorder, acute coronary syndrome, severe heart failure, confirmed or suspected lower-limb fracture preventing mobilization, and those requiring palliative care will be excluded.

Baseline assessor completed:

Baseline assessment of the primary and secondary measures (described above) *and additionally include*

1. An assessment of receptive/expressive aphasia the Sheffield Screening Test for Acquired Language Disorders ([Syder 1993](#_ENREF_44)) **(**Appendix 2**)**
2. The Mini Mental State Examination ([Folstein, Folstein et al. 1975](#_ENREF_14)) to assess cognitive function. **(**Appendix 3**).**
3. Star Cancellation test (Appendix 4)
4. Modified Rankin Scale (Appendix 5)

Table 1: Assessment Schedule. *All measures are completed by blinded assessor except the self report log, which participants complete weekly, themselves.

| Outcome measure | Baseline | Post Intervention (8 weeks post-randomisation) | Follow Up (3 months post-randomisation) |
| --- | --- | --- | --- |
| Gait speed | X | X | X |
| Time & number of steps to turn 90° | X | X | X |
| Timed up and Go | X | X | X |
| Fugl-Meyer | X | X | X |
| Berg Balance Scale | X | X | X |
| Functional ambulation classification | X | X | X |
|  |  |  |  |
| SF 12 | X | X | X |
| Self report log* | X | X | X |
| Falls Efficacy Scale | X | X | X |
| Pedometer |  | During treatment |  |
| Sheffield Screening Test | X |  |  |
| MMSE | X |  |  |
| mRS | X |  |  |
| Star Cancellation test | X |  |  |
| Patient demographics | X |  |  |

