### Expected duration of participant participation

During the active treatment period, participants will attend the outpatient rehabilitation setting for 1hr., two times weekly for 8 weeks. Participants will then be assessed at follow up 3 months after baseline.

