### Removal of participants from therapy or assessments

Participants may permanently discontinue treatment if safety is considered to be at risk e.g. development of comorbidities preventing ability to participate in the treatment, the participant fails to comply with treatment or they withdraw consent. In all of these situations outcome data will continue to be sought at the usual planned time points when the participant and safety permits. Measures will be taken within 5 days following consent and treatment or they will not be included in the dataset at that time point. Given the aims of the study are to determine the numbers of patients who do not complete the allocated treatment, thus dropping out of the study, and determine the reasons for dropping out, withdrawn participants will not be replaced.

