### PROCEDURES FOR MISSING, UNUSED AND SPURIOUS DATA

Every effort will be made to reduce the proportion of missing data items through trial quality assurance procedures.

In terms of the dealing with any missing data we believe that imputation will not be appropriate for this case since as mentioned before this is a pilot study designed to obtain answers for a definite trial. Hence a tabulation of missing data and looking for reasons of any missing data will be a better method for this study. Using this information it will be possible to see what the majority of the missing data is (if any) and can then look for alternative procedures to minimise this further for the definitive trial.

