### DEFINITION OF POPULATION ANALYSED

**Full analysis set:** All randomised participants who participated in at least one treatment and for whom at least one post-baseline assessment of the primary endpoint is available.

Primary and Secondary endpoints will be analysed using the full analysis set, defined as all randomised participants for whom a post-baseline assessment of the primary endpoint is available, that is, in accordance with the ‘intention to treat’ (ITT) principle.

This pilot study is designed to assess the feasibility of conducting a large scale trial and so no safety summaries will be necessary to be performed.

No per protocol analysis is envisaged therefore no assessment of protocol deviations will be performed.

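### After an adverse event one section removes the participant from the study while another keeps seeking outcomes, and no text says which rule prevails (minor)

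*Protocol*

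**What the plan says.** Two sections of the Protocol cover a participant who has to stop the trial treatment for a safety reason.

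- **Removal of participants from therapy or assessments** lists safety (with newly developed comorbidity as the example), failure to comply and withdrawn consent as grounds for stopping treatment permanently. It then states: "In all of these situations outcome data will continue to be sought at the usual planned time points", subject to the participant and safety.
- **Participant removal from the study due to adverse events** states: "Participants will be removed from the study following an AE if treating medical team indicate" that the person can no longer tolerate walking practice. Both heading and sentence speak of the study, not of treatment. Follow-up is not mentioned, and there is no reference to the other section.

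Three further places bear on the consequence. The Primary Objective defines completeness as the percentage of patients with no missing values in the outcome assessments. The full analysis set consists of treated, randomised participants "for whom at least one post-baseline assessment of the primary endpoint is available". Missing data are not imputed; the plan is a "tabulation of missing data and looking for reasons of any missing data".

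**The concern.** Walking practice is the trial treatment in all three arms. A participant who cannot tolerate it after an adverse event is therefore also someone whose treatment stops for safety. One section says to keep assessing this person; the other says the person leaves the study. A therapist handling an adverse event would naturally turn to the adverse-event section, which is also the more categorical of the two.

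This is a rule of conduct, so it cannot be left to a statistical analysis plan: visits that were never made cannot be recovered at analysis. Completeness of outcome data and drop-out are primary objectives of this pilot. The trial management section names incomplete data, questionnaires above all, as a medium-level risk. The usual-care section says therapist contact is matched across groups partly to limit differential loss to follow-up. A literal removal rule would work against those aims and would mix loss caused by the protocol with loss caused by the measures themselves.

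**Working it through.** There is no protocol figure to reproduce. The check sets the two rules side by side and then asks what changes for the participant concerned.

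**1. Overlap of the two rules**

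| | Removal from therapy or assessments | Removal due to adverse events |
| --- | --- | --- |
| Trigger | Safety at risk, for example comorbidity that prevents treatment | Cannot tolerate walking practice after an AE |
| Consequence | Treatment stops | Leaves the study |
| Outcomes | Still sought when participant and safety permit | Not mentioned |

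The second trigger lies inside the first. The sections on endpoints, duration, safety, missing data, analysis sets and trial termination contain no rule of precedence.

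**2. When it can happen.** The exposure is the treatment period: "participants will attend the outpatient rehabilitation setting for 1hr., two times weekly for 8 weeks". Removal would then come before the first post-baseline visit, headed "Post Intervention (8 weeks post-randomisation") in Table 1, and before the 3-month visit.

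**3. Measures affected.** Table 1 marks eight assessor-completed measures at both post-baseline visits (the self-report log is left out): gait speed, 90-degree turn, Timed Up and Go, Fugl-Meyer, Berg, functional ambulation classification, SF-12 and Falls Efficacy Scale.

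- Scheduled after baseline: 8 × 2 = 16 per participant.
- Needing no walking test: at least Fugl-Meyer, SF-12 and Falls Efficacy Scale, so 3 × 2 = 6.

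Literal removal loses at least those 6, and up to 16 if the walking tests were also safe.

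**4. Completeness endpoint.** It is all-or-nothing for each participant.

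- Walking tests unsafe: gait speed, turning and Timed Up and Go are missing under either rule. The participant is incomplete both ways, so the change is 0.
- Every measure still possible at both visits: the participant is complete under one rule and incomplete under the other. With 60 participants (Synopsis and Randomization sections), the change is 1/60 = 1.7 percentage points for one such participant, 2/60 = 3.3 for two and 3/60 = 5.0 for three. These counts are illustrative assumptions.

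For scale, assume 54 of 60 complete: 90.0%, exact (Clopper-Pearson) 95% interval 79.5% to 96.2%. One removal of the second kind gives 53/60 = 88.3%, interval 77.4% to 95.2%. The first interval is 96.2 − 79.5 = 16.7 points wide, about ten times the 1.7-point shift.

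**5. Full analysis set.** Membership needs at least one post-baseline assessment of the primary endpoint, taken here as gait speed. If no walk is safe at either visit, the participant is outside the set under both rules. Literal removal changes membership only if at least one walk could have been done.

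**The case against.** The strongest reply is that the adverse-event section is loose wording for stopping treatment. The protocol uses such language elsewhere: the very paragraph that continues follow-up describes "the numbers of patients who do not complete the allocated treatment, thus dropping out of the study", and goes on to call these people withdrawn. On that usage only one section says what happens to outcome data, and it should govern. This is plausible and may well be what was meant. It remains an inference, because the adverse-event section neither says so nor points to the other section.

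A second reply is that the proviso about participant and safety reconciles the two. It excuses a test that is unsafe, but it does not end participation, and two of the measures at stake are questionnaires.

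A third reply stands in large part: anyone unable to tolerate walking practice may also be unable to do the walking tests. A reader might infer that every adverse-event removal costs 1.7 points of completeness and a place in the full analysis set. The documents do not support that. Both change only for someone who cannot manage practice sessions, with their 20 to 30 minutes of walking, but can still be tested safely. Few adverse events are expected, and no formal testing or efficacy assessment is planned.

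A reader might also infer that early stoppers are excluded in any case, because of this rule: "Measures will be taken within 5 days following consent and treatment or they will not be included in the dataset at that time point". If the window ran from the last session attended, someone stopping at the end of week 3 (an assumed example) would be seen at week 8, (8 − 3) × 7 = 35 days later and 30 days outside it. That is only one reading. The preceding sentence ties those who stop to the usual planned time points, and Table 1 counts from randomisation. It is a separate question of clarity and not part of this conflict.

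**Conclusion.** The conflict is real and minor. Two sections give different instructions for the same participant and neither yields to the other. The certain loss under literal removal before the 8-week visit is data from at least three measures at two visits that the protocol elsewhere wants collected. The effect on the completeness endpoint is at most 1.7 percentage points per participant who could otherwise have been fully assessed, and zero for the rest; the analysis-set effect is limited in a similar way. The documents do not give the number of such participants, and they do not show that any site would read the sentence literally. They also give no basis for claiming a bias between arms.

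**What to change.** Retitle the adverse-event section *Withdrawal from trial treatment due to adverse events* and replace its sentence with, for example: *A participant whose treating medical team judges, after an AE, that walking practice can no longer be tolerated will be withdrawn from trial treatment. Outcome assessments continue at the planned 8-week and 3-month time points, as described under Removal of participants from therapy or assessments, when the participant and safety permit.*

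Optionally, and as a separate clarification, add one clause to Removal of participants from therapy or assessments: for those who stop early, the 5-day window runs from the planned 8-week time point.

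The missing-data section and the analysis-set definition need no change, since reasons for missing data are already to be tabulated. No visits are added. The cost is a little assessor time for participants who have stopped treatment, plus a minor amendment. The ethics section lets purely logistical or administrative changes take effect at once with the ethics committee informed; if the sponsor does not class this as such, approval comes first.

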# ETHICAL AND REGULATORY ASPECTS

## ETHICS COMMITTEE AND REGULATORY APPROVALS

The trial will not be initiated before the protocol, informed consent forms and participant and GP information sheets have received approval / favourable opinion from the Research Ethics Committee (REC), and the respective National Health Service (NHS) Research & Development (R&D) department. Should a protocol amendment be made that requires REC approval, the changes in the protocol will not be instituted until the amendment and revised informed consent forms and participant and GP information sheets (if appropriate) have been reviewed and received approval / favourable opinion from the REC and R&D departments. A protocol amendment intended to eliminate an apparent immediate hazard to participants may be implemented immediately providing that the REC are notified as soon as possible and an approval is requested. Minor protocol amendments only for logistical or administrative changes may be implemented immediately; and the REC will be informed.

The trial will be conducted in accordance with the ethical principles that have their origin in the Declaration of Helsinki, 1996; the principles of Good Clinical Practice, and the Department of Health Research Governance Framework for Health and Social care, 2005.

## INFORMED CONSENT AND PARTICIPANT INFORMATION

The process for obtaining participant informed consent or assent and parent / guardian informed consent will be in accordance with the REC guidance, and Good Clinical Practice (GCP) and any other regulatory requirements that might be introduced. The investigator or their nominee and the participant or other legally authorised representative shall both sign and date the Informed Consent Form before the person can participate in the study.

The participant will receive a copy of the signed and dated forms and the original will be retained in the Trial Master File. A second copy will be filed in the participant’s medical notes and a signed and dated note made in the notes that informed consent was obtained for the trial.

The decision regarding participation in the study is entirely voluntary. The investigator or their nominee shall emphasize to them that consent regarding study participation may be withdrawn at any time without penalty or affecting the quality or quantity of their future medical care, or loss of benefits to which the participant is otherwise entitled. No trial-specific interventions will be done before informed consent has been obtained.

The investigator will inform the participant of any relevant information that becomes available during the course of the study, and will discuss with them, whether they wish to continue with the study. If applicable they will be asked to sign revised consent forms.

If the Informed Consent Form is amended during the study, the investigator shall follow all applicable regulatory requirements pertaining to approval of the amended Informed Consent Form by the REC and use of the amended form (including for ongoing participants).

## RECORDS

### Case Report Forms

Each participant will be assigned a trial identity code number, allocated at randomisation, for use on CRFs other trial documents and the electronic database. The documents and database will also use their initials (of first and last names separated by a hyphen or a middle name initial when available) and date of birth (dd/mm/yy).

CRFs will be treated as confidential documents and held securely in accordance with regulations. The investigator will make a separate confidential record of the participant’s name, date of birth, local hospital number or NHS number, and Participant Trial Number (the Trial Recruitment Log), to permit identification of all participants enrolled in the trial, in accordance with regulatory requirements and for follow-up as required

CRFs shall be restricted to those personnel approved by the Chief or local Principal Investigator and recorded on the ‘Trial Delegation Log.’

All paper forms shall be filled in using black ballpoint pen. Errors shall be lined out but not obliterated by using correction fluid and the correction inserted, initialled and dated.

The Chief or local Principal Investigator shall sign a declaration ensuring accuracy of data recorded in the CRF.

### Source documents

Source documents shall be filed at the investigator’s site and may include but are not limited to, consent forms, current medical records, laboratory results and records. A CRF may also completely serve as its own source data. Only trial staff as listed on the Delegation Log shall have access to trial documentation other than the regulatory requirements listed below.

### Direct access to source data / documents

The CRF and all source documents, including progress notes and copies of laboratory and medical test results shall made be available at all times for review by the Chief Investigator, Sponsor’s designee and inspection by relevant regulatory authorities.

## DATA PROTECTION

All trial staff and investigators will endeavour to protect the rights of the trial’s participants to privacy and informed consent, and will adhere to the Data Protection Act, 1998. The CRF will only collect the minimum required information for the purposes of the trial. CRFs will be held securely, in a locked room, or locked cupboard or cabinet. Access to the information will be limited to the trial staff and investigators and relevant regulatory authorities (see above). Computer held data including the trial database will be held securely and password protected. All data will be stored on a secure dedicated web server. Access will be restricted by user identifiers and passwords (encrypted using a one way encryption method).

Information about the trial in the participant’s medical records / hospital notes will be treated confidentially in the same way as all other confidential medical information.

Electronic data will be backed up every 24 hours to both local and remote media in encrypted format.

# QUALITY ASSURANCE & AUDIT

## INSURANCE AND INDEMNITY

Insurance and indemnity for trial participants and trial staff is covered within the NHS Indemnity Arrangements for clinical negligence claims in the NHS, issued under cover of HSG (96)48. There are no special compensation arrangements, but trial participants may have recourse through the NHS complaints procedures.

## TRIAL CONDUCT

Trial conduct will be subject to systems audit of the Trial Master File for inclusion of essential documents; permissions to conduct the trial; Trial Delegation Log; CVs of trial staff and training received; local document control procedures; consent procedures and recruitment logs; adherence to procedures defined in the protocol (e.g. inclusion / exclusion criteria, correct randomisation, timeliness of visits); adverse event recording and reporting; accountability of trial materials and equipment calibration logs.

## TRIAL DATA

Monitoring of trial data shall include confirmation of informed consent; source data verification; data storage and data transfer procedures; local quality control checks and procedures, back-up and disaster recovery of any local databases and validation of data manipulation.

Entries on CRFs will be verified by inspection against the source data. A sample of CRFs (10% or as per the study risk assessment) will be checked on a regular basis for verification of all entries made. In addition the subsequent capture of the data on the trial database will be checked. Where corrections are required these will carry a full audit trail and justification.

Trial data and evidence of monitoring and systems audits will be made available for inspection by REC as required.

